### Confounders

Habitual physical activity levels will be collected before, after the 6-month intervention and at 3-month follow-up using an accelerometry-based method – *ActiGraph GT9X Link* -, for 7 consecutive days [87]. Participants will be instructed to wear the accelerometer attached to an elastic belt at all times except when sleeping, bathing, swimming or other water activities. Data will be collected in 100 Hz epochs and a minimum of 10-h on at least 4 days (1 weekend) will be considered valid data. Physical activity data will be processed using *Actilife* software (*Actigraph LLC* Pensacola, FL) and summarized as time spent in sedentary, light, moderate to vigorous physical activity.

### Statistical analysis plan

Descriptive statistics will be expressed as mean and standard deviation (SD) or as median and interquartile range (IQR) for continuous variables. Categorical variables will be expressed as frequency and percentages. Normal distribution will be analyzed by the Kolmogorov-Smirnov test with Lilliefors’ (K–S) significance correction and normal probability plots. Statistical comparisons at baseline characteristics will be performed using t-test or Mann–Whitney U-test for continuous variables and Chi-squared test or Fisher’s test for categorical variables.

Age, gender, level of education, dementia type/stage, and other variables will be considered as potential confounders and adjustments will be performed in accordance to detect differences between experimental and control group.

The primary effect parameter will be the difference in the SPPB and ADAS-Cog tests between the experimental and control groups, considering the two different moments of evaluation (baseline and after 6-month of intervention). An analysis of variance (ANOVA) test with repeated measures adjusted for potential confounders will be performed for the intervention-related effects. When a significant F value is obtained, Bonferroni post hoc procedures will be used to evaluate pairwise differences. Additionally, mixed effects models will be performed in order to identify potential predictive factor associated with the changes in primary and secondary outcomes from baseline, post-intervention and over the 3-months detraining period.

A multivariable regression analysis will be performed in order to explore the association between cardiovascular and blood-markers, and cognition.

Statistical analyses will be conducted with the SPSS IBM Statistical Software version 25.0 (SPSS, Inc., Chicago, IL) for Windows with a significance level of *p* < 0.05.

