### Trial design

This study is a multicenter quasi-experimental controlled trial with a parallel design, that will be conducted in a wide-ranging public and private settings (e.g., daycare centers and local community centers) in the Porto metropolitan area, Portugal. Participants will be recruited from community programs, daycare centers, psychiatric hospitals and clinics (i.e., outpatients followed within psychiatry or neurology specialists), Alzheimer’s and caregivers’ associations, municipalities, local journals, and social media. Advertisements will be made via phone calls, emails, informative flyers and presential and online meetings. In order to motivate and clarify concerns about the exercise sessions, a short MT session will be provided to exemplify and illustrate a typical session for individuals with dementia.

Eligible participants and caregivers will receive a complete explanation of the study purposes, risks and procedures. Following the best ethical procedures, informed consent will be obtained from interested dementia participants and from their main caregivers/legal representatives/significant person. After agreeing to participate and according to personal availability, participants will be allocated into a 6-month MT intervention (IG) or into a social activity group (CG) (see Fig. 1). All CG participants will be offered the possibility to participate in an exercise program after the end of the study cycle.

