Aerobic endurance will be attained with low impact exercises at 60–65% of HRMax implemented in two 5-min periods. Intensity will increase progressively with increasing duration and HR until reaching 2 periods of 10 continuous minutes of exercise at 75 to 80% of HRmax. Sessions will be monitored using heart rate monitors [47], and whenever possible, the Modified Borg Scale of Perceived Exertion will be applied.

Exercise professionals will registry adverse events (such as pain or fatigue) and number of falls during exercise sessions to provide information on safety of the MT program. Finally, attendance to sessions will be recorded and reasons for absences the will be catalogued [48].

Although this is not a dyadic intervention, caregivers will be included in each session as class members, but focus will be directed to individuals diagnosed with dementia. Along with the novelty of this strategy, this approach will facilitate dementia patients’ participation once their transportation, motivation, and involvement are dependent of their caregivers [49, 50]. Additionally, caregivers’ participation will also be determinant to deal with behavioral and psychological symptoms of dementia patients [46].

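### Arms are formed by personal availability, but the adjustment set is open-ended and its rule unclear, so correction for that selection is not assured

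*Protocol article*

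**What the plan says.** **Allocation.** Under Trial design: "This study is a multicenter quasi-experimental controlled trial with a parallel design". Groups are formed after consent: "according to personal availability, participants will be allocated into a 6-month MT intervention (IG) or into a social activity group (CG").

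**Caregivers.** In the exercise-training section, where the article explains why caregivers join the sessions, it says of participants that "their transportation, motivation, and involvement are dependent of their caregivers".

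**Baseline tests.** In the Statistical analysis plan: "Statistical comparisons at baseline characteristics will be performed using t-test or Mann–Whitney U-test for continuous variables", with chi-squared or Fisher tests for categorical variables.

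**Adjustment.** The next paragraph reads "Age, gender, level of education, dementia type/stage, and other variables will be considered as potential confounders", and continues "adjustments will be performed in accordance to detect differences between experimental and control group".

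**Primary model.** A repeated-measures ANOVA of SPPB and ADAS-Cog at baseline and 6 months, adjusted for potential confounders. The Sample size section instead bases the calculation on ANCOVA.

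**Other covariates.** The Confounders section and Table 1 list accelerometer-measured activity at baseline (T0), 6 months (T1) and follow-up (T2). The Control group section makes co-interventions during the trial covariates.

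**Collected at baseline but not named as covariates.** Comorbidities (Trial design) and the caregiver measures in Table 1 (CarerQol, and caregiver distress from the NPI).

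**The concern.** Exercise sessions run twice a week and control sessions monthly. Availability for one or the other may well differ with caregiver support, health and place, and each of these could affect function and cognition. Without randomisation, the adjustment set is the main protection against such selection.

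As written, the plan weakens that protection in three ways:

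- The list is open, so covariates can be settled after results are seen.
- The rule can be read as making adjustment depend on baseline tests, which often miss imbalances of relevant size.
- The baseline outcome is differenced in the repeated-measures analysis and not conditioned on. Regression to the mean and differing trajectories therefore stay in the group-by-time effect.

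The abstract's Discussion expects evidence on efficacy, and that expectation depends on how well selection is handled.

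**Working it through.** **Inputs from the article (Sample size):** 55 per group, SPPB difference 1 point, SD 2.1, alpha 0.05, power 80%, dropout 25%.

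**Assumed:** equal SD at both times; baseline-to-6-month correlation ρ of 0.5 to 0.8; true imbalance of 0.2 to 0.4 SD in a confounder; correlation c of that confounder with SPPB change of 0.3 to 0.5.

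**1. The plan's own figure**
- Two-sided, without using baseline: n = 2 × 2.1² × (1.96 + 0.84)² / 1² ≈ 69.2, so 70 per group. After dropout, 70 / 0.75 = 94, not 55.
- ANCOVA multiplies the variance by (1 − ρ²). With ρ = 0.64: 69.2 × (1 − 0.41) ≈ 40.9, so 41; 41 / 0.75 ≈ 55. The stated figure is thus obtained if baseline is conditioned on and ρ is about 0.64, which is not stated.
- A one-sided test also gives 55, but with no dropout allowance, so the derivation is not certain.
- At ρ = 0.64 a change analysis multiplies the variance by 2(1 − ρ) = 0.72. That gives 50 per group before dropout, and about 72% power with 41 completers per group.

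**2. Baseline tests as a screen**

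Probability that a two-sided t-test with 55 per group is non-significant (1 − power):

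| True imbalance | Non-significant |
|---|---|
| 0.2 SD | 82% |
| 0.3 SD | 66% |
| 0.4 SD | 45% |

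**3. Bias if the variable is left out of the planned analysis**

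The group-by-time effect compares changes, so bias = imbalance × c × SD of change, where SD of change = 2.1 × √(2(1 − ρ)).
- ρ = 0.5: SD of change = 2.1. Bias = 0.3 × 0.3 × 2.1 = 0.19 to 0.3 × 0.5 × 2.1 = 0.32.
- ρ = 0.8: SD of change = 1.33. Bias = 0.3 × 0.3 × 1.33 = 0.12 to 0.3 × 0.5 × 1.33 = 0.20.
- Range: 0.12 to 0.32 point.

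Equivalently, bias = imbalance × 2.1 × (correlation with SPPB at 6 months − correlation at baseline). Equal correlations give zero; a gap of 0.1 gives 0.3 × 2.1 × 0.1 = 0.06. The range 0.12 to 0.32 needs gaps of 0.12 / 0.63 = 0.19 to 0.315 / 0.63 = 0.50, so its upper end is demanding.

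**4. Whether conditioning on baseline matters**

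For a baseline SPPB imbalance of 0.3 × 2.1 = 0.63 point, the change-based and baseline-adjusted estimates differ by (1 − ρ) × 0.63. That is 0.13 at ρ = 0.8 and 0.32 at ρ = 0.5. Neither estimate is automatically unbiased in a non-randomised comparison, so the primary one has to be named in advance.

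**The case against.** Several stronger readings are tempting, and the article does not support them.

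- **That baseline activity is ignored.** It is listed as a confounder in the Confounders section and Table 1. What stands is that no text restricts adjustment to its baseline value.
- **That baseline SPPB and ADAS-Cog are left out of the analysis.** They are one of the two repeated measures, so stable level differences drop out of the group-by-time effect. What stands is that they are not conditioned on, while the sample size assumes ANCOVA.
- **That adjustment certainly follows significant baseline differences.** The sentence can equally mean adjusting in order to detect group differences, and the ANOVA sentence carries no significance condition. On that reading the list is still open.
- **That selection stays uncorrected.** The open wording could admit availability or caregiver factors, and stage or education may partly stand in for them.
- **That caregivers determine the arm.** The article says only personal availability. The caregiver sentence explains why caregivers join sessions, so the link is an inference, though a plausible one.
- **That the bias is 0.19 to 0.32 point.** That range takes correlations of 0.3 to 0.5 with the 6-month score and suits a post-score comparison. In the planned analysis the bias depends on correlation with change and may be near zero.

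It is also fair to say that an article may leave the full covariate list, site handling and sensitivity analyses to a fuller document. Their absence alone would be no finding. But the article does state an adjustment rule, and that rule is open and ambiguous where a non-randomised design depends on it most.

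**Conclusion.** The point holds in a limited form: correction for selection by availability is not assured. This rests on the article's own text: allocation by availability, an open covariate list, an unclear rule placed after baseline tests, and a baseline outcome treated one way in the sample size and another in the analysis.

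The non-detection figures (66% at 0.3 SD, 82% at 0.2 SD) are firm arithmetic, but they matter only if the rule is applied as a screen. The bias range of 0.12 to 0.32 SPPB point, up to about a third of the target difference, is conditional. It assumes a 0.3 SD imbalance, a correlation with change of 0.3 to 0.5, ρ of 0.5 to 0.8, and a variable neither adjusted for nor represented by the named covariates. The article gives none of these values, and the bias is near zero if the variable relates equally to SPPB at both times. This should be changed, but it does not show that the trial's result will be wrong.

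**What to change.** 1. State that adjustment does not depend on baseline p-values.
2. Fix one compact, closed set of T0 covariates: baseline value of the outcome (ANCOVA, in line with the Sample size section), age, sex, education, dementia type (collapsed), CDR, comorbidity count, T0 accelerometer activity, site, and one caregiver measure already collected at T0.
3. Keep T1 and T2 activity, and co-interventions begun during the trial, out of the primary model, since treatment may affect them. Report them descriptively.
4. Keep the repeated-measures change analysis as a sensitivity analysis, and add an overlap-weighted propensity-score analysis with the same covariates.
5. Word the conclusion as an adjusted, non-randomised comparison.

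**Cost.** Mostly analysis text. Degrees of freedom are lost with about 82 completers (110 × 0.75 = 82.5), so the set must stay short, with categories of dementia type and site merged where sparse. New caregiver items such as transport or co-residence would be useful but optional. Recruitment began in September 2018, so they could be collected at true baseline only for participants not yet enrolled. No set of measured covariates removes confounding by what was not measured.

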### Data management and confidentiality

An identification code will be attributed to each participant with common designation for IG and CG. The correspondence list between name and ID will be stored in a lockable cabinet at the Principal Investigator office located at the Research Centre, and separately of the report forms and evaluation instruments. Any personal information such as name, address or other identification data will not be collected nor registered. Data will be entered into an electronic database by two authorized researchers. The management and any statistical treatment will be only conducted after the authorization of the Principal Investigator. Data will be destroyed after 10 years of the end of intervention, and electronic data will be deleted 5 years after the last scientific publication.

### Ethics and dissemination

The study protocol was approved by the Ethical Committee of the Faculty of Sports of the University of Porto (Ref CEFADE22.2018). All participants and caregivers/legal representatives/significant person will be asked to sign an informed consent. Data confidentiality and anonymity will be guaranteed in all phases of the study. All procedures performed will follow the ethical standards of the institutional and/or national research committee and the 1964 Helsinki Declaration and its later amendments or comparable ethical standards. We intend to disseminate study results via presentations in national and international conferences and manuscripts in peer reviewed scientific journals. Additionally, we will promote seminaries directed for the entire community and especially for the participants, caregivers, health care professionals and organizations. We also intend to disseminate important results through local public media. Participants and caregivers will be informed individually of study results via synthetized reports.

## Discussion

This study describes the protocol of a quasi-experimental controlled trial of a 6-month MT intervention for IwD comprehended on “Body & Brain” project. Some innovative aspects of this trial are worthy highlighting. For instance, we believe that tailored, individually adjusted, and sustained MT led by a well-trained exercise specialist, may positively impact physical and cognitive function of people living with dementia, independently of their type/stage of dementia. Another innovative aspect of this trial will be the inclusion of caregivers in the exercise sessions. This is of particular relevance for improving the dynamic relationship between caregiver and IwD, to increase participants’ adherence to the intervention and the caregivers’ awareness regarding positive nonpharmacological interventions in dementia care [88]. Thus, by including caregivers in exercise sessions, we expect that both the caregiver and the care-recipient will remain active after the end of the trial. This intervention may also positively impact IwD neuropsychiatric symptoms, and therefore improve quality of life. Informal caregivers’ quality of life and ability to cope with BPSD’s may also be improved, especially if they exchange experiences with other caregivers. Finally, at a molecular level, we aim to examine how exercise can positively impact the neurotropic and inflammatory factors, as well as the endothelial function, commonly altered in IwD [89]. Our findings will give much needed insights about its impact on the pathophysiology of dementia and help to improve the current evidence regarding exercise as non-pharmacological intervention in IwD.

Some challenges in this trial must be recognized. First, due to the study design and the dementia paradigm in the Portuguese population, we anticipate a heterogeneous sample, under(/mis) diagnosed and with many different comorbidities [90, 91]. Secondly, IwD tend to be sedentary for most of the day and practice low-intensity physical activities [92], which is particularly concerning in the Portuguese paradigm, where older population are highly sedentary [93], Therefore, authors expect some difficulties during recruitment. Nevertheless, this project is expected to raise awareness on exercise intervention for IwD among caregivers, institutions that provide care services for older adults, policy makers and general community. We expect to contribute to the cultural change regarding the therapeutic options to manage dementia. Moreover, our goals goes along with the WHO recommendations for the functional health era in which exercise has a decisive role [4]. Finally, presuming that our data will show that IwD can respond positively to a moderately challenging tailored MT exercise, our project can be a significant step to move towards in what concerns older adults exercise prescription. Authors believe that this research may contribute to disseminate and generalize exercise prescription among this population in order to prevent disability and attenuate or delay the cognitive decline. As long as the cure for dementia remains to be achieved, and the pharmacological limitations of treatment remain, we cannot neglect the global and coadjuvant role MT exercise may have as a non-pharmacological treatment.

### Trial status

The trial commenced recruitment in September 2018 and is currently in process. Recruitment will cease when the expected number of participants has been achieved.

## Data Availability

Data sharing is not applicable to this article as no datasets were generated or analyzed during the current study.

## Abbreviations

AD: Alzheimer’s Disease
ADAS-Cog: Alzheimer’s Disease Assessment Scale - Cognitive
ADL: Activities of Daily Living
ANOVA: Analysis of Variance
BDNF: Brain-derived Neurotrophic Factor
BPSD: Behavioral and Psychological Symptoms of Dementia
CarerQol: Care-related Quality of Life instrument
CDR: Clinical Dementia Rating
cfPWV: Carotid-femoral Pulse Wave Velocity
CG: Control Group
CLIA: Chemiluminescent Immunoassay
CRP: C-reactive Protein
DSM-5: Diagnostic and Statistical Manual of Mental Disorders Fifth Edition
DSM-IV-TR: Diagnostic and Statistical Manual of Mental Disorders Fourth Edition – Text Revision
DXA: Dual Energy X-ray Absorptiometry
ELISA: Enzyme-linked Immunosorbent Assay
HbA1c: Glycated Hemoglobin
HDL-C: High-Density Lipoprotein Cholesterol
HPLC: High Performance Liquid Chromatography
HRmax: Maximum Heart Rate
ICD-10: International Statistical Classification of Diseases and Related Health Problems-10th Revision
IG: Intervention Group
IGF-1: Insulin Like Growth Factor 1
IL-6, IL-8, IL-10: Interleukin 6, 8, 10
IwD: Individuals with Dementia
IADL: Instrumental Activities of Daily Living
IQR: Interquartile Range
LDL-C: Low-Density LipoproteinCholesterol
MMP-9: Metalloproteinase-9
MMSE: Mini Mental State Examination
MT: Multicomponent Training
NINCDS-ADRDA: National Institute of Neurological and Communicative Disorders and Stroke - Alzheimer’s Disease and Related Disorders Association
NPI: Neuropsychiatric Inventory
QoL-AD: Quality of Life-Alzheimer’s Disease
SD: Standard Deviation
SFT: Senior Fitness Test
sICAM-1: Intercellular Adhesion Molecule-1
SPPB: Short Physical Performance Battery
sVCAM-1: Vascular Cell Adhesion Molecule-1
TC: Total Cholesterol
TG: Triglycerides
TMT: Trail Making Test
TNF-alfa: Tumor Necrosis Factor-alfa
VEGF: Vascular Endothelial Growth Factor
WHO: World Health Organization
